#### Sample size

Sample size calculations were conducted in G * Power (version 3.1). A 120 kcal (500 kJ) difference in *ad libitum* test meal energy intake and a 10 mm change in visual analogue scale (VAS) appetite ratings have previously been considered physiologically relevant differences^(8,51)^. To allow for 20–25 % dropout, a sample size of 180 participants (45 per group) is sufficient to detect these differences between groups, allowing for 10 % variance on a within participant sd of change in *ad libitum* test meal energy intake of 143 kcal ^(36,52)^, and for VAS of about 13 mm, observed in our unpublished data, similar to others^(36)^, at 80 % power and significance at *P* < 0·05.

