#### Cardiorespiratory fitness, physical function and strength

Cardiorespiratory fitness will be estimated using a usual-paced 400 m walk test^(75)^. Physical function will be assessed by Short Physical Performance Battery (SPPB) combining the assessment of balance, gait speed and repeated chair stands tests^(76)^. Individual test scores and overall score will be calculated. Leg strength of the dominant leg will be assessed as the maximum value from three trials using a seated leg extension dynamometer to determine maximal voluntary isometric contraction of the knee extensors. Handgrip strength will be assessed as the maximum value from three trials with a Jamar hydraulic grip strength dynamometer, with the participant in a seated position and arm rested on the table at a 90-degree angle using the dominant hand, unless contraindicated.

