### Data management and statistical analysis plan

All data will be collected on questionnaires and record sheets in a de-identified manner using a participant ID number and stored securely according to General Data Protection Regulation (2018)^(84)^ at each site, with electronic data double-entry into a central electronic database stored and backed up at one site (Ireland). The trial coordinating centre Principal Investigators will have access to the full dataset across all sites. Study site Principal Investigators will have direct access to the dataset at their own site and will have access to data from other sites by request. Anonymised data will be made available to other researchers on reasonable request after the main trial manuscript is published.

There are no plans for interim study analysis. After completion of the study data collection, data will be checked and cleaned using descriptive statistics and data visualisation. Outcome data will first be analysed according to the intention-to-treat principle, using a random coefficients generalised linear mixed model for primary and secondary end points. The effects of time, the two interventions and their interaction (following the 2 × 2 factorial design of the trial) and sex will be included as fixed effects. Participant ID and study site will be included as random effects. Residuals will be tested for normality and transformation applied where required, or where the structure of the data is inherently non-normal. 95 % CI will be reported where applicable. Per-protocol analyses and mediation analyses will be conducted to examine to what extent compliance and potential mediating mechanisms explain the impact on the primary and secondary end points. For primary pre-planned contrasts, significance will be accepted as *P* < 0·05. Where groups of secondary outcomes are analysed, the significance level will be adjusted by Bonferroni correction according to the number of responses in the analysis. A correlation matrix will be constructed to assess relationships between outcome variables. Missing data will not be imputed in the primary analysis. Intention-to-treat analyses will be based on the *as-observed* population.

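### Single-step Bonferroni within secondary-outcome groups is valid but less efficient than it need be; Holm holds the same error rate and never rejects less

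*Protocol article*

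**What the plan says.** All of the following is in the protocol article.

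- **The rule.** Under *Data management and statistical analysis plan*, the adjustment applies "Where groups of secondary outcomes are analysed", and then "the significance level will be adjusted by Bonferroni correction according to the number of responses in the analysis". With m responses in a group, each test is made at 0.05/m. No step-down procedure is named. The groups and their sizes are not listed, which a condensed article may leave to a fuller plan.
- **The model.** The same section analyses the data "using a random coefficients generalised linear mixed model for primary and secondary end points". The fixed effects are described as "The effects of time, the two interventions and their interaction (following the 2 × 2 factorial design of the trial) and sex". Each secondary response therefore has three intervention terms: personalised diet (PD), physical activity (PA) and PD x PA.
- **Related responses.** Under *Cardiorespiratory fitness, physical function and strength*, for the Short Physical Performance Battery (SPPB), "Individual test scores and overall score will be calculated". Leg strength, handgrip strength and the 400 m walk are listed beside it.

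**The concern.** The procedure and its divisor are fixed in the text, so this is a choice that can be assessed and not a detail left out. Bonferroni compares every p-value in a group with 0.05/m, even after some responses have already been declared significant. Holm relaxes the threshold step by step after each rejection and has the same family-wise guarantee.

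The difference matters most when several responses in a group move together. That is plausible here for the strength and function measures, which the exercise programme targets directly. What is at stake is some power on secondary outcomes. The validity of the planned tests is not in question.

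**Working it through.** **Inputs**

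- Rule: 0.05/m per test, from the statistical section. Two-sided testing is assumed, because sidedness is not stated.
- Completers: the *Sample size* section gives 180 participants and 20–25% dropout. At 25%, 180 x 0.75 = 135. A main effect in the 2 x 2 design compares halves, 135/2 = 67.5, so 68 v 68.
- Assumed, because the article gives no value for secondary outcomes: standardised effect d = 0.5, correlation 0.4 between responses, group size m = 6.

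The article gives no power figure for secondary outcomes, so there is none to reproduce.

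**Step 1. The planned rule is valid.** By the Bonferroni inequality, m tests at 0.05/m have a family-wise error of at most m x 0.05/m = 0.05, under any dependence. With independent tests and m = 6 it is 1 − (1 − 0.05/6)^6 = 0.049. In simulation at correlation 0.4 it is 0.044.

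**Step 2. Power under Bonferroni.** The noncentrality is d/√(2/68) = 0.5/0.1715 = 2.915. The critical value at 0.05/6 = 0.0083 is 2.638. Power is Φ(2.915 − 2.638) = Φ(0.277) = 61%. Unadjusted, it would be Φ(2.915 − 1.960) = 83%.

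**Step 3. Holm.** Order the p-values from smallest to largest and compare them in turn with 0.05/m, 0.05/(m − 1), …, 0.05, stopping at the first failure. For m = 6 the thresholds are 0.0083, 0.0100, 0.0125, 0.0167, 0.0250 and 0.0500. None is below the Bonferroni threshold, so nothing is lost. If m₀ null hypotheses are true, the first false rejection can only occur at a threshold of 0.05/m₀ or less. The family-wise error is therefore at most m₀ x 0.05/m₀ = 0.05, again under any dependence.

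**Step 4. Size of the gain.** Simulation with 200,000 draws per row, m = 6, correlation 0.4:

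| Responses truly affected | Power per true effect, Bonferroni | Holm | Family-wise error, Bonferroni | Holm |
|---|---|---|---|---|
| 1 of 6 | 61% | 61% | 0.038 | 0.042 |
| 2 of 6 | 61% | 62% | 0.031 | 0.039 |
| 3 of 6 | 61% | 64% | 0.023 | 0.036 |
| 4 of 6 | 61% | 66% | 0.016 | 0.033 |
| 6 of 6 | 61% | 72% | no true nulls | no true nulls |

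No draw had a response rejected by Bonferroni and not by Holm.

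**Step 5. Sensitivity to the assumptions.** Suppose instead that each true effect has 80% unadjusted power and responses are independent. With every response affected, power rises from 66% to 75% (m = 3), 59% to 70% (m = 5) and 50% to 61% (m = 10). With half affected (3 of 6 or 5 of 10) the gain is about 3 points. With one affected it is 0.2 points or less.

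**Step 6. What the 5% covers.** If all three intervention terms are tested, a group has 3m tests at 0.05/m. With no true effects and independent tests, the chance of at least one false positive is 1 − (1 − 0.05/m)^(3m) = 0.140 for m = 3, 5 or 10. It falls to 0.130–0.135 at correlation 0.3 and 0.100–0.121 at 0.6. Under the global null, Holm applied separately to each effect leaves this figure unchanged.

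**The case against.** **Bonferroni is valid, so this is only a preference.** It is valid, and the article says nothing false here. Bonferroni also has simple matching confidence intervals, and the article says that 95% intervals will be reported. This sets the priority. It does not remove the point: at the same error rate, one procedure never rejects less than the other.

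**The gain may be small.** This stands. With few responses affected it is one point or nothing. The 11-point gain needs all six affected, at an effect size the article does not give. The SPPB total and component scores illustrate overlapping responses, but the article does not say that they share a group.

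**A stronger reading is tempting: that the divisor is wrong.** A reader might infer that dividing by m fails because three intervention effects are tested per response, giving about 14% and not 5%. The documents do not support calling this an error. The rule is stated as an adjustment over responses, and for each effect it does that. Nowhere is 5% promised jointly over PD, PA and PD x PA. Treating the effects of a factorial design as separate questions is a recognised choice. The three tests are themselves inferred from the model terms, since the article does not list the secondary tests.

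Pooling all 3m tests would also cost power. With m = 5 and 80% unadjusted power, the present rule gives 59%; Holm over all 15 tests gives 46–54%. Pooling is a trade-off and not a required correction.

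**Conclusion.** The point holds as one of efficiency. The planned Bonferroni adjustment controls error as stated, but Holm in the same families would control it equally and never reject less. With six responses, 68 v 68 completers, d = 0.5 and correlation 0.4, the gain in average power per true effect runs from nil (one response affected) through 3 points (three affected) to 11 points (all six affected). The effect size, correlation and group size are assumptions. That Holm never does worse depends on none of them.

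The figure of about 14% over three effects describes what the rule covers, assuming independence and that all three terms are tested. It breaks no commitment in the article. The primary outcomes and the sample size of 180 are untouched, so the priority is low.

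**What to change.** Keep the families as they are: the responses in a group, taken separately for each intervention effect. Replace single-step Bonferroni with Holm's step-down procedure within each family. Add one reporting sentence saying that 5% is held per effect and that, if PD, PA and PD x PA are all tested, the chance of at least one false positive in a group with no true effects is about 14% for independent tests. Pooling all 3m tests is not needed.

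The cost is wording only, with no new data. The one real downside is that confidence intervals matching Holm are less simple than Bonferroni intervals. A practical course is to report unadjusted 95% intervals, labelled as such, beside Holm-adjusted p-values.

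The *Trial status* section puts the last test visit in July 2024. The change should therefore be dated and recorded before outcome results by group are seen, or reported as made afterwards if analysis has begun.

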### Ethics and dissemination

Ethical approval has been received from the Human Research Ethics Committees at each trial centre and the trial registered on ClinicalTrials.gov (NCT05608707). The study will be reported according to the Consolidated Standards of Reporting Trials (CONSORT) guidelines for parallel-group randomised trials. Participant informed consent will be obtained in writing prior to study enrolment (online Supplemental Appendix 6). Adverse events will be recorded and reported to the relevant ethics committee. Participants are informed they may withdraw with no obligation to provide a reason. If participants choose to provide a reason, the reason will be recorded. Amendments to the trial protocol including changes to study objectives, design, participant population, sample sizes, study procedures or significant administrative aspects are updated on the trial registry and submitted as an amendment for ethical approval at each site.

Trial results will be disseminated through websites, reports, presentations, peer-reviewed journal articles and workshops to a wide audience of stakeholders in the area of healthy ageing including researchers, healthcare providers, policymakers, industry and older adults. Topics and authors proposed for peer-reviewed publication as a journal article will be circulated to the trial principal investigators of the coordinating centres and the consortium principal investigators, with authorship based on established authorship guidelines^(85)^.

## Discussion

The APPETITE trial is the first RCT to evaluate the impact of PD and PA alone or in combination on appetite and related health outcomes in older adults. The PD intervention involves the participant incorporating two PPF powder supplements into the diet and receiving personalised dietary advice to achieve defined daily energy and protein targets. The PA intervention involves supervised resistance exercise classes twice per week and home-based walking three times per week.

Although previous studies have investigated the effects of protein supplementation, alone or with PA on sarcopenia-related outcomes^(86,87)^, nutritional outcomes, particularly appetite, have received little attention. Alongside plant protein supplementation, the inclusion of fibre, identified as lacking in diets of many older adults and appealing to those with poor appetite^(26,27,35,88)^, is a novel aspect of the present study. Furthermore, previous supplementation studies have focused primarily on providing a supplement, without considering usual dietary habits and preferences, thus not following a personalised approach which is recommended by consensus guidelines^(2)^.

The PPF supplements that are provided to participants as part of the PD intervention were developed based on prior research and initial data from earlier work packages as part of the wider APPETITE project^(49)^. The supplements provided consist of a blend of plant proteins to optimise the amino acid content and reduce the limitations associated with providing a single plant protein source^(89)^. The PPF supplements were selected from a range of six blends developed for the trial, initially based on results from sensory testing among older adults to optimise compliance, and subsequently from assessment of peripheral amino acid appearance following consumption.

As noted in the methods section, during the initial months of the trial, the inclusion criteria requiring participants to have a SNAQ score </= 14 was removed. This criterion was adjusted for several reasons including difficulty encountered in recruitment and acknowledging both findings from work package 1 of the wider APPETITE project and limited validation studies of SNAQ as an assessment of appetite *per se*. Work package 1 involved semi-structured interviews with older adults with ‘poor appetite’ as defined by SNAQ (</=14). A key finding was that despite their SNAQ score, many participants did not recognise they had a poor appetite or were reluctant to acknowledge their appetite loss^(90)^. This difficulty in self-identifying appetite loss may likely contribute to challenges in recruiting community-dwelling older adults with a ‘poor appetite’. While the inclusion of specific ‘appetite loss’ criteria may be more feasible in a clinical setting (where appetite loss is more widespread and more pronounced) as part of regular patient screening and appropriate for drug trials, such criteria may be less applicable for lifestyle intervention trials targeting community-dwelling older adults. In addition, reduced appetite and energy intake occurs in healthy older compared with younger adults^(10)^, and is not defined by SNAQ score specifically. Consequently, the APPETITE trial will include older adults not defined by a specific ‘appetite status’ at baseline.

A key strength of the design is the multi-centre design, thereby enhancing the generalisability of findings and potential future implementation of the interventions. Further strengths include the 2 × 2 design, allowing for the impact of PD and PA separately and in combination to be elucidated. In addition, given additional facilities and expertise available at some centres (such as muscle biopsy and analysis), insight into important additional outcomes will be obtained in subsamples. The integration of comprehensive assessment, including body composition, gut microbiome, blood biomarkers, functional, metabolic and health-related outcomes, will give insight into mechanisms contributing to any changes observed.

The time required to improve some of the outcomes assessed is unclear and may require a longer duration than the 12-week intervention in the APPETITE RCT; however, effects of protein supplementation and exercise on appetite have previously been demonstrated in 12-week trials across various populations^(36,91)^.

Due to the nature of the intervention, one limitation is that it is not possible to blind participants to treatment allocation. An additional limitation is the lack of blinding of researchers who are involved in both the administration of the intervention and data collection due to logistical constraints. However, data will be analysed anonymously by a blinded researcher to minimise detection bias.

In summary, the APPETITE multi-centre RCT will provide novel insight on the impact of PD (incorporating PPF products), PA and their combination on appetite, and other nutritional, functional, clinical and metabolic outcomes in community-dwelling older adults. This will advance knowledge on how these interventions influence appetite, dietary intake and nutritional status and contribute to future research in the field. This will ultimately inform guidelines to contribute to a better nutritional status and quality of life for older Europeans.

### Trial status

This protocol is version 4 registered on 29/9/2023. Recruitment began in September 2022 and finished in April 2024, with the last participant completing their final test visit in July 2024.
